### Control group

The participants will be seen at the Outpatient Cardiology Clinic of the Institute of Cardiology. Children in the control group will be seen every two weeks, receiving orientation about correct eating habits and the need to increase physical activity. This type of care is performed routinely, but a specific day will be reserved for these patients in the outpatient clinic.

Each child will receive a booklet with written guidelines. Targets will be set with the child, to promote a change of attitudes and motivation specifically focused on possibly inappropriate food choices detected.

At the end of the study, the intervention activities will be offered to all participants in the control group.

### Outcomes

The primary outcomes will be the differences between the intervention and control groups with regard to changes in dietary habits, knowledge and physical activity of the participants, from the beginning to the end of follow-up for children and adults. The secondary outcomes will be the differences between the intervention and changes in body mass index, waist circumference, systolic and diastolic blood pressure, total cholesterol, LDL-cholesterol, HDL-cholesterol, triglycerides, glucose, complete blood count and C-reactive protein, both in children and their parents. Figure 2 presents a timeline for assessing the outcomes.

**Figure 2 Fig2:**
[figure not shown]
**Study timeline for intervention and assessment of outcomes.**

### Evaluation of outcomes

Time schedules for both groups is presented in Figure 2. All results will be evaluated at the beginning and at the end of follow-up, in all participants in the intervention and control groups.

A general evaluation questionnaire will be administered to the parents, to identify personal details of parents and children, breastfeeding time, age of introduction of complementary foods, early and family history. Evaluation tools used with the children will include the “TDPA” and the “Cardiokid” questionnaires.

The TDPA (Typical day of physical activity questionnaire) is an illustrated and structured questionnaire, developed in the Portuguese language by a group of researchers from Brazil, with the purpose of obtaining information about a typical day of physical activity [41]. The questionnaire was developed for children aged 7 10 years and is evaluated by a sum of scores: children reaching a total lower than 36 classified as “less active”, from 37 to 58 as “intermediate”, and from 59 to 141 classified as “most active” [41].

The Cardiokid questionnaire was developed in the portuguese language with the aim of evaluating knowledge about healthy habits and risk factors for cardiovascular disease [42]. It presents 12 illustrated and colourful questions, with three alternative answers represented by faces: “smiling” (good for the heart), “sad” (bad for the heart) and “neutral” (I don’t know). The sum of right answers determines the level of knowledge: “excellent knowledge” (11 to 12), “good knowledge” (eight to 10) and “insufficient knowledge” (below seven correct answers) [42].

The blood pressure will be measured with the appropriate size cuff. Three readings, each about two minutes apart, will be taken on the right arm, in a sitting position, with the arm supported at heart level, after a 10 minutes rest. The average of the last two measurements will be used for the analysis. For children, the systemic blood pressure will be considered abnormal if the systolic and/or diastolic measurement is greater than or equal to the 95th percentile for gender, age and height percentile [42-45]. For adults, values of systolic blood pressure ≥ 140 mmHg and/or diastolic blood pressure ≥ 90 mmHg [46] will be considered abnormal.

Body weight and height will be measured in duplicate by one of the researchers. Patients (children and parents) will be asked to remove shoes and heavy coats for this measurement. Nutritional status will be assessed by calculation of body mass index (BMI), with use of the Anthro Plus ® program, according to the guidelines of the World Health Organization [47,48]. BMI cut-off points for defining overweight and obesity in children will be percentile > 85 and percentile > 95, respectively, according to WHO-2006/2007 [49]. For adults, the BMI will be obtained through the relationship between total body weight in kilograms divided by height in meters squared, and will be classified according to the World Health Organization - eutrophy (BMI between 18.5 and 24.9 kg/m^2^), overweight (between 25 and 29.9 kg/m^2^), obesity I (between 30 and 34.9 kg/m^2^), obesity II (between 35 and 39.9 kg/m^2^) and obesity III (≥40 kg/m^2^) [50,51].

For children and adults, waist circumference will be measured with a measuring tape at the midpoint between the last palpable rib and the top of the iliac crest, where there is a greatest amount of visceral tissue. In children, waist circumference will be classified according to the National Health and Nutrition Examination Survey, 2003–2006 (NHANES 2003–2006), with cut-off points in the 90th percentile, according to gender and age. For adults, waist circumference cut-off points for increased cardiovascular risk will be considered as ≥94 cm for men and ≥80 cm for women, according to the World Health Organization [52].

Blood will be collected for analysis of total cholesterol, LDL-cholesterol, HDL-cholesterol and triglycerides, glucose, complete blood count and C-reactive protein after a 12 h fasting. The biochemist performing the assay will be blinded to the identity of the participants. Analyses will be conducted with an automatic enzyme technique, with Roche® kits (Brazil).

Lipid profile abnormalities will be defined as: total cholesterol ≥ 200 mg/dL; LDL-cholesterol ≥ 130 mg/dL; HDL-cholesterol < 40 mg/dL; triglycerides ≥ 100 mg/dL (age 0–9 years) or ≥ 130 mg/dL (age 10–19 years). Glucose levels will be considered abnormal as ≥ 100 mg/dL [43-45]. All the above cut-off points, which are very similar to the cut-off points of the Brazilian guidelines [44], were proposed in the Expert Panel on Integrated Guidelines for Cardiovascular Health and Risk Reduction in Children and Adolescents: Summary Report, of the American Academy of Pediatrics (AAP) [45].

For adults, lipid profile abnormalities will be defined as: total cholesterol ≥ 240 mg/dL; LDL-cholesterol ≥ 190 mg/dL; HDL-cholesterol < 40 mg/dL) and triglycerides ≥ 200 mg/dL). Glucose will be considered abnormal if ≥ 100 mg/dL [44,45].

### Sample size

Sample size was estimated considering a possible reduction of 20 g/dL and standard deviaton of 29,9 on total cholesterol in the intervention groups, similar to the observed in another Brazilian study [53]. The sample size was thus estimated as 37 patients in each group, considering a significance level of 0,05 and power of 0,80, with the aid of an online sample size calculator (Russ Lenth) USA [54]. Considering the outcome “BMI change”, to detect a standardized difference of 1,0 as observed by “Effects of a School-based Weight Maintenance Program for Mexican-American Children: Results at 2 years, with a bilateral alpha of 0,05 and power of 0,8, we estimated the need of a sample size of 17 participants per group [55].

### Randomization

The randomization will be performed with the aid of a sequence generated on the website www.randomization.com [56], after input of the total number of patients required, number of arms and number of blocks. The randomization in blocks was chosen because the total number of patients will probably not be available at the same date in the beginning of the study. If there is the need to apply the intervention in more than one small group in order to reach the total sample required, it is more appropriate the these patients will be evenly distributed regarding date of inclusion. The list will include ten random blocks, each with ten patients, aiming at ensuring equal distribution between the arms of the study. Allocation will be concealed by placing the randomized designations in white envelopes, which will be sealed and opened only after inclusion of the patient in the study. All steps described above will be undertaken by a third party researcher, not directly involved in the study.

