## Methods/Design

### Study design

The study is planned as a randomized controlled, outcome evaluator-blinded parallel prospective clinical trial. This protocol is based in the CONSORT and SPIRIT statements for reporting of clinical trials and protocols [39,40]. A total of 74 children will be recruited. After the initial assessment, children will be randomized to either the intervention or the control groups with 1.1 allocation (Figure 1). The study setting is the “Instituto de Cardiologia do Rio Grande do Sul”, a cardiology hospital in south Brazil.

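### With every block fixed at ten and allocation visible to care staff, up to about 12 of 74 allocations could be deduced before inclusion; opening envelopes by wave would remove most of the opportunity

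*Protocol article*

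**What the plan says.** Under Randomization, the protocol article fixes one block size throughout: "The list will include ten random blocks, each with ten patients". Under Study design, "children will be randomized to either the intervention or the control groups with 1.1 allocation" (the ratio is evidently 1:1), so each block has five places per arm. No stratification is described, and the setting is a single hospital, so all allocations come from one sequence.

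Blocking was chosen because "the total number of patients will probably not be available at the same date in the beginning of the study". The same section foresees running the intervention in more than one small group.

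Two safeguards are stated. The allocations are kept in sealed envelopes, "opened only after inclusion of the patient in the study", and a researcher from outside the study carries out all these steps.

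On blinding, Study design describes a "randomized controlled, outcome evaluator-blinded parallel prospective clinical trial", and Evaluation of outcomes adds that the biochemist does not know whose samples are being assayed. Care staff and families cannot be blinded. One arm attends weekly family workshops and receives text messages. In the other, "Children in the control group will be seen every two weeks, receiving orientation about correct eating habits", on a day reserved for them in the outpatient clinic.

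**The concern.** A sealed envelope hides its own content. It does not hide what follows by subtraction. Once one arm has used its five places in a block of ten, every remaining place in that block belongs to the other arm. Anyone who knows the block size and has followed the allocations so far knows those places before the next envelope is opened. Opening the envelope only after inclusion does not help if the allocation could be worked out before inclusion.

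What is at stake is selection at entry. Families come through announcements and referrals at different dates, so staff may have some say in when a family is included. Someone who expects the next place to be a workshop place could hasten or delay a family that looks motivated. Motivation is not among the listed measurements, so a baseline table might not show this, and intention-to-treat analysis does not correct it. Physical activity, one of the primary outcomes, is taken from a questionnaire and could plausibly be affected.

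**Working it through.** The article gives no figure for predictability, so there is none to reproduce.

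**Inputs**
- Block size 10, the same for all blocks (Randomization).
- Ratio 1:1, so m = 5 places per arm (Study design).
- Total 74 children (Study design). This is 2 × 37 from Sample size; a two-sided t test for a difference of 20 with SD 29.9 at 80% power needs 36.07 per group, which rounds up to 37.
- Assumptions not taken from the article: enrolling staff know the block size, see every earlier allocation in list order, and enrol one child at a time.

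**Chance that a place is certain in advance.** A block of ten has C(10,5) = 252 equally likely arrangements. Place k + 1 is certain if one arm has already filled its five places within the first k. That holds in 2 × C(k,5) arrangements.

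| Place | Arrangements in which it is certain | Chance |
|---|---|---|
| 1 to 5 | 0 | 0% |
| 6 | 2 × C(5,5) = 2 | 0.8% |
| 7 | 2 × C(6,5) = 12 | 4.8% |
| 8 | 2 × C(7,5) = 42 | 16.7% |
| 9 | 2 × C(8,5) = 112 | 44.4% |
| 10 | 2 × C(9,5) = 252 | 100% |

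The sum is 420/252 = 1.67 per block. The closed form 2m/(m + 1) = 10/6 = 1.67 agrees.

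**For 74 children.** There are seven full blocks and four places of an eighth. Those four places add nothing, so the expected count is 7 × 1.67 = 11.7, and 11.7/74 = 15.8%. This is an average over possible lists; a particular list may have more or fewer.

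**Best guess.** Always guessing the arm with more places left is right for 6.53 of 10 in a full block (65.3%). Simulated over 74 places it is 64.8%.

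**Other block schemes.** Fixed blocks of 4, 6 or 8 would make 33%, 25% or 20% of places certain, so ten is not a small block. For mixed sizes, 4,000 lists of 74 were simulated, with sizes drawn at random and staff assumed to know the set of sizes but not their order.

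| Scheme | Certain in advance | Best guess correct |
|---|---|---|
| Fixed 10 | 15.8% (11.7 of 74) | 64.8% |
| Random 6, 8, 10 | 1.6% (about 1.2 of 74) | 66.2% |

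Mixing the sizes removes nearly all the certainty. It does not reduce guessing, which becomes very slightly easier.

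**The case against.** The strongest reply is that the article establishes none of the three conditions behind the figure.

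- **Knowledge of the block size.** An outside researcher handles the list, and nothing says that recruiters were told the size. The size is printed in the article, but that does not show recruiters knew it while enrolling. Whether it was withheld is a detail that an article may leave to the full protocol.
- **Sight of past allocations in order.** No section says that the people who include families also run workshops or clinics. Seeing who attends does not by itself give the order within a block.
- **One at a time.** Project timelines runs from 1 October 2013 to completed analyses in March 2014, at most about 26 weeks. Eleven weeks of participation leave at most about 15 for recruitment, and small groups are foreseen. Batches are therefore plausible, and within a batch few earlier allocations would be visible.

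All of this stands. It makes the figure an upper bound. It does not remove the weakness, because the single block size and the visibly different arms are stated features of the plan and the safeguards named do not prevent deduction.

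It is also fair that ten is a fairly large block for 74 children, that fixed blocks with sealed envelopes are conventional, and that the article already places the initial assessment before randomization. These points limit the severity.

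Two stronger readings are tempting. A reader might infer that the trial is simply open-label; that fits families and care staff, but evaluator blinding is stated. A reader might also infer that all primary outcomes are self-reported and driven by motivation. The Cardiokid questionnaire is a knowledge test scored by right answers, and the article gives no figure linking motivation to any outcome.

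**Conclusion.** The point holds as a conditional one of low severity. If enrolling staff know the block size, follow allocations in order and enrol singly, an average of 1.67 of every 10 allocations, or about 12 of 74, can be known before inclusion. With batch enrolment or recruiters separate from care staff the number is lower, and the article does not allow it to be estimated.

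A reader might infer that staff did know one allocation in six, or that the trial is biased. The document supports neither: it does not show that anyone predicted or acted on an allocation, and the size of any resulting bias cannot be derived from it.

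**What to change.** **Main change, for the remaining enrolment.** Complete consent, baseline assessment and the order of entry for every child in a wave before the third party opens any of that wave's envelopes. This fits the staggered small groups that the Randomization section foresees, and it removes most of the chance to act on a prediction. Some remains where a wave ends partway through a block, because the imbalance carries into the next wave. The cost is a short written rule and a longer wait for the first families in each wave.

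**Secondary change, for unused list positions.** The third party prepares a continuation with block sizes in random order, for example 6, 8 and 10, and does not disclose them to the study team. This brings certain allocations down to about 2% but does not lower the overall best-guess rate, so it should not replace the wave rule. The cost is a new list, and arm numbers within a workshop group may be slightly less even. The article names only total patients, arms and number of blocks as inputs to the randomization website, so the third party should check whether it can produce mixed sizes or whether another tool is needed. Recruitment has already begun, so the benefit depends on how much of the list is still unused.

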### Data analysis

Data will be analyzed according to the intention-to-treat approach, with the Statistical Package for the Social Sciences (SPSS) version 20.0. Continuous variables will be expressed as means and standard deviations, and categorical variables, in absolute and relative frequencies. Groups will be compared with the Student’s *t* test for continuous variables and Chi-square test for categorical variables. Analysis of variance (ANOVA) for repeated measures will be used for intra and inter-group comparisons. Since this is a short duration trial and risks are considered minimal, we do not plan to perform interim analysis. The significance level adopted will be 5%.

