### Project timelines

The recruitment of the participants began on October 1, 2013. Analyses are expected to be completed, with discussion of the first results, in March 2014.

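### Blocking balances the arms on date of inclusion, but the named tests include no intake term; adding one, together with an allowance for workshop group, would recover some power if outcomes differ by intake period

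*Protocol article*

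**What the plan says.** The Randomization section explains that blocks were chosen because the children will probably not all be available at the same time. If the programme has to be run in more than one small group, "it is more appropriate the these patients will be evenly distributed regarding date of inclusion". The mechanism follows: "The list will include ten random blocks, each with ten patients".

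The Data analysis section names the between-arm comparisons: "Groups will be compared with the Student’s *t* test for continuous variables and Chi-square test for categorical variables". It adds a repeated-measures ANOVA for comparisons within and between groups, without listing its factors. No block, intake cohort or date appears.

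On timing, Project timelines states "The recruitment of the participants began on October 1, 2013" and expects the analyses to be finished in March 2014. Each child takes part for eleven weeks. The intervention is given in group workshops; the control arm is seen in the outpatient clinic, which the Abstract describes as individual care.

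**The concern.** Blocking by order of entry makes intake period a factor that the design balances. Variation between intake periods is then largely removed from the difference between arms. A two-sample t test still counts that variation as error, and neither it nor a plain chi-square test can carry an intake term. If intake periods differ in outcome, the test runs below its nominal 5% from this source, and part of the benefit of the balancing is lost.

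Such differences are plausible. Diet and physical activity are primary outcomes, and children who enter at different times from October onwards are followed over different eleven-week windows. At stake is a modest amount of precision in a trial of 74 children.

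**Working it through.** **Inputs from the protocol article.** Sample size section: "a possible reduction of 20 g/dL and standard deviaton of 29,9 on total cholesterol in the intervention groups", "considering a significance level of 0,05 and power of 0,80", and "The sample size was thus estimated as 37 patients in each group". The printed unit cancels. Sidedness is not given for this calculation; the BMI calculation beside it is two-sided ("with a bilateral alpha of 0,05 and power of 0,8"). Randomization section: blocks of ten, so 74 children fill seven blocks and four places of an eighth.

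**Assumed, because the document gives no value.** The share *s* of outcome variance due to intake period (0 to 0.30), and the correlation ρ within workshop groups in the intervention arm. Total SD is held at 29.9, and the last, incomplete block is taken as 2:2.

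**Step 1: the plan's own figure.** The normal approximation gives 2 × (1.96 + 0.842)² × (29.9/20)² ≈ 35.1, so 36 per arm. With the noncentral t, power is 0.799 at 36 and 0.810 at 37. The stated 37 is reproduced as the two-sided t-test answer. The standard error is 29.9 × √(2/37) = 6.95.

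**Step 2: intake effects alone.** With intake balanced, the true standard error is 6.95 × √(1 − *s*), while the t test goes on estimating a value close to 6.95.

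- *s* = 0.05: 6.95 × √0.95 = 6.77
- *s* = 0.10: 6.95 × √0.90 = 6.59
- *s* = 0.20: 6.95 × √0.80 = 6.22

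Simulation (40,000 trials per setting; eight blocks or three cohorts as the intake factor) gives:

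| Share *s* | Unadjusted type I error, 8 blocks / 3 cohorts | Power, 8 blocks: unadjusted → adjusted | Power, 3 cohorts: unadjusted → adjusted |
|---|---|---|---|
| 0 | 5.1% / 5.1% | 80.6 → 80.5% | 80.7 → 80.6% |
| 0.05 | 4.4% / 4.5% | 81.9 → 83.0% | 82.1 → 82.9% |
| 0.10 | 4.0% / 4.5% | 82.8 → 85.0% | 83.6 → 85.2% |
| 0.20 | 3.1% / 3.7% | 84.0 → 88.7% | 85.2 → 88.5% |
| 0.30 | 2.4% / 3.2% | 85.5 → 92.1% | 87.4 → 92.4% |

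The gain is about 1 point at 5%, about 2 points at 10%, and 3.4 (three cohorts) to 4.7 (eight blocks) at 20%. A separate simulation of 8,000 trials per setting agrees closely; there the cost at *s* = 0 was 0.3 points. Unadjusted power never falls below 0.80.

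**Step 3: add clustering by workshop group in the intervention arm only.** Take three groups of 15, 15 and 7 intervention children, with *s* = ρ = 0.05. The variance of the difference is 29.9² × {(1 − *s* − ρ)/37 + ρ(15² + 15² + 7²)/37² + (1 − *s*)/37} = 894.0 × (0.0243 + 0.0182 + 0.0257) = 61.0, so the true standard error is 7.81 (simulated 7.82).

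- **Three groups:** the unadjusted t test reports 6.86 on average, and type I error is 8.6%. With the intake term alone the reported value falls to 6.71, and type I error rises to 9.3%.
- **Eight groups, same values:** reported 6.93 against a true 7.08. Type I error is 5.4% unadjusted and 6.1% with the intake term alone.

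**The case against.** The strongest case against raising this has four parts.

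- **The loss is conditional.** No between-intake variance is given, and running several intervention groups is itself only a contingency in the Randomization section. This stands. It is why the size is shown as a range that includes zero.
- **A large share is not evident.** From 1 October to the end of March is about 26 weeks; less eleven weeks of participation, intake lasts at most about 15 weeks. The primary outcomes are changes from baseline, so stable differences between cohorts cancel and only differing trends matter. The SD used is for total cholesterol, a secondary outcome. This also stands, and makes the 5% to 10% rows easier to defend than the 20% to 30% rows.
- **Nothing planned fails.** Under intake effects alone the test is conservative and keeps its power. This stands too.
- **A condensed article may leave model terms to a fuller plan.** This stands only in part. The ANOVA's factors are not listed, so one cannot say that it omits intake. But the article does name the t test and the plain chi-square test, and these do not use the factor on which the allocation was balanced.

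A reader might go further and infer that the trial's confidence intervals will be too wide. The document does not support that. Group delivery in one arm can make the same tests anti-conservative, as Step 3 shows under values as permissible as those of Step 2.

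**Conclusion.** The mismatch between the Randomization and Data analysis sections is real, and its consequence is modest. If intake period explains part of the outcome variance, the named tests lose about 1 point of power at a 5% share, 2 at 10% and 3 to 5 at 20%; if it explains none, adjusting costs half a point or less. These figures rest on assumed shares, on balance within intake periods, and on the cholesterol SD taken as the total SD. The sample size of 37 per arm is unaffected. This is a worthwhile gain in efficiency, not an invalidating error. The net direction of error in the planned intervals cannot be stated from the document, because workshop clustering acts the other way and may dominate.

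**What to change.** In the Data analysis section:

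1. Compare continuous outcomes between arms with a linear model containing group and intake cohort. Fix one definition of cohort in advance, for example the start-date cohort; the term drops out if all children start together.
2. In the same model, allow for workshop group in the intervention arm, for example by a random effect present in that arm only. Do not add the intake term alone. Workshops run on three days of the week, so workshop groups need not coincide with intake cohorts, and both should be recorded.
3. For categorical outcomes, use a Mantel-Haenszel chi-square stratified by intake cohort. It makes no allowance for workshop group, so where an outcome exists both as a score and as a category, the score should carry the comparison.

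The intake term costs 2 error degrees of freedom out of 72 with three cohorts, or 7 with eight blocks. With few workshop groups, the allowance for clustering will widen intervals where clustering is present, which is its purpose. Inclusion date and block should already be on record for every child, and workshop group is fixed by attendance, so no new measurements or participants are needed.

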### Interventions

The goal of the intervention is to improve health habits of students and their families. Children and their families will receive intervention for eleven weeks. The materials will be developed around the following key messages:Consequences of inadequate eating habits;Recommendation of adequate intake of nutrients;Health promotion strategies.

The materials will be designed for a fun, entertaining appearance. The meetings will be practical and playful, including culinary workshops, games and homework assignments. All materials were developed targeting this specific cultural environment, based on our 10-year work with children in the Public Health System in Brazil. We have researched materials from other countries, but we felt that developing our own materials would benefit other groups in similar situations. We also plan to involve the children in the creation of materials during the workshops. Materials are fun and playful because they are mostly based in popular games and ludical activities. Workshops will be held in 3 different days of the week, from 6 PM to 7:30 PM. The setting is a health school located in the complex of Instituto de Cardiologia, with an ample room to accommodate children and families. All the members of the family that wish to participate together with their children will be invited. Children and caretakers will attend the workshops together, except in the days when the cooking workshops will take place at the cooking lab (days 3 and 8). During the 9 weeks of workshops, text messages will be sent twice a week, on Mondays and Saturdays (total of 18 messages). Message content will be related to practical tips for a healthy lifestyle. Some examples are presented in Table 1.

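### Only the intervention arm is treated in workshop groups, but the sample size and all named tests assume independent children; if groups induce correlation, standard errors are too small and power is overstated

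*Protocol article*

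**What the plan says.** Under Study design, 74 children are randomized individually and equally to two arms. The Abstract describes the intervention as weekly group meetings. The Interventions section adds: "Workshops will be held in 3 different days of the week, from 6 PM to 7:30 PM". The Randomization section allows for several groups, but conditionally: "If there is the need to apply the intervention in more than one small group in order to reach the total sample required". The number of groups is never fixed. Under Control group, control children attend an outpatient clinic every two weeks and targets are set with each child.

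The Background treats the group as part of the mechanism: problems are shared, solutions are sought together, and peer support is ranked among the most valuable kinds of support. The Interventions section adds a closed social-media group.

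For the analysis, the protocol names a Student's t "test for continuous variables and Chi-square test for categorical variables", and then: "Analysis of variance (ANOVA) for repeated measures will be used for intra and inter-group comparisons". The level is 5%. The Sample size section assumes "a possible reduction of 20 g/dL and standard deviaton of 29,9 on total cholesterol" and arrives at "37 patients in each group, considering a significance level of 0,05 and power of 0,80". None of these places mentions workshop group or a design effect.

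**The concern.** After allocation, an intervention child shares facilitators, sessions and a peer group with other intervention children. A control child does not. If that shared experience moves outcomes together, 37 intervention children carry less information than 37 independent ones.

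The t test and chi-square test take no account of this. Repeated-measures ANOVA handles correlation within one child over time, not between children in the same workshop. Permuted blocks balance the arms over calendar time but do not repair standard errors.

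At stake are confidence intervals that are too narrow, a type I error above the nominal 5%, and a stated power that the trial does not have. The primary outcomes (dietary habits, knowledge and physical activity) are the kind that a shared group could plausibly move together.

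**Working it through.** **Inputs from the protocol.** 37 children per arm; difference 20 and SD 29.9 for total cholesterol (only the ratio matters here); alpha 0.05; target power 0.80.

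**Assumed inputs.** The ICC within a workshop group (0.01 to 0.10 shown) and the number of groups. Three groups, sized 13, 12 and 12, is the case suggested by the three weekdays; other counts are shown for range.

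**Step 1: reproduce the plan's figure.** The standardized difference is 20/29.9 = 0.669. The two-sided two-sample t calculation for independent children gives 37 per arm with power 0.810. The normal approximation gives 36, and power 0.820 at 37. The stated 37 is therefore the independent-children figure, with no allowance for clustering.

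**Step 2: variance under partial nesting.** In the intervention arm the design effect is DE = 1 + (m − 1) × ICC, where m is the size-weighted mean group size. For three groups, m = (13² + 12² + 12²)/37 = 457/37 = 12.35. Only one arm is inflated, so true SE / naive SE = √((DE + 1)/2). At ICC 0.05, DE = 1 + 11.35 × 0.05 = 1.57 and the ratio is √(2.57/2) = 1.13.

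**Step 3: type I error and power.** Type I error of the naive test is about 2 × [1 − Φ(1.96/ratio)]. Power with the correct SE is Φ(0.669/(√(2/37) × ratio) − 1.96). For three groups:

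| ICC | DE | SE ratio | Type I error, formula | Type I error, simulated | Power |
|---|---|---|---|---|---|
| 0 | 1.00 | 1.00 | 5.0% | 5.0% | 82% |
| 0.01 | 1.11 | 1.03 | 5.7% | 5.7% | 80% |
| 0.02 | 1.23 | 1.06 | 6.3% | 6.2–6.5% | 78% |
| 0.05 | 1.57 | 1.13 | 8.4% | 8.4–8.5% | 72% |
| 0.10 | 2.14 | 1.25 | 11.7% | 11.5–11.9% | 63% |

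**Step 4: other group counts.** Type I error of the naive t test at ICC 0.01 / 0.05 / 0.10:

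- two groups: 6.1% / 10.4% / 15.6%
- five groups: 5.3% / 7.0% / 8.9%
- seven groups: 5.3% / 6.3% / 7.6%
- one group of 37: 7.2% / 15.5% / 24.7%

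With one group, the group effect cannot be told apart from the treatment effect.

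**Step 5: cost of few groups.** The powers in Step 3 ignore the loss of degrees of freedom. A simulated comparison of three group means with the controls, using Satterthwaite degrees of freedom at ICC 0.05, has about 56% power, and its own type I error is still slightly high at about 6%.

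**The case against.** The strongest reply is that the inflation is conditional. Allocation is by individual child, so if the programme and its groups affect nobody, sorting children into workshops after allocation cannot upset the t test. A simulation with clusters that existed before individual randomization, at ICC 0.10, rejected 5.0% of the time. Inflation needs the workshops themselves to create correlation, through group dynamics, facilitators or shared circumstances. This stands: a flat statement that the 5% level is not held goes too far. But a protocol that relies on group process is poorly placed to assume zero correlation.

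The ICC and the group count are both assumptions. At ICC 0.01 with three to seven groups the excess is under one percentage point. The protocol also does not say that each family keeps to one weekday. This stands too, and is why a range is given.

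The power figures concern total cholesterol, a secondary outcome. That is the outcome on which the plan sized the trial; the protocol gives no planning figures for the primary ones.

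Details of random effects are often left to an analysis plan. Here, however, the article names the tests, and none of them allows for workshop group.

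A reader might also infer that self-selected extra relatives enter the adult comparisons, from "All the members of the family that wish to participate together with their children will be invited". That sentence is about attendance. The Abstract, the last workshop entry in Table 2 and the Outcomes section name guardians or parents as the adults studied, and nothing says that further relatives are measured. The documents do not support that reading.

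**Conclusion.** The point holds in conditional form. The design is partially nested, and the sample size and named analyses treat it as if it were not. Any positive correlation induced by the workshops makes the standard errors too small. The estimate itself is not biased by group effects that average to zero; its uncertainty is understated.

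With three groups, type I error runs from about 5.7% (ICC 0.01) to nearly 12% (ICC 0.10). With seven groups it stays between 5.3% and 7.6%. The planned 0.80 power for total cholesterol is overstated by little at ICC 0.01 and by a good deal at 0.10 (63% with three groups, before the degrees-of-freedom loss). All of this rests on an assumed ICC and an assumed group count.

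**What to change.** 1. Record the workshop group to which each intervention child is assigned, including non-attenders, since the analysis is by intention to treat.
2. State the expected number of groups.
3. For continuous outcomes, replace the t test and repeated-measures ANOVA with a linear mixed model: fixed effects for arm and baseline value, a random workshop-group effect in the intervention arm only, and Satterthwaite degrees of freedom. Mixed models of this kind can be fitted in SPSS, the package already named.
4. Restate power over ICC 0 to 0.10, without enrolling more children.
5. State the limits. With about three groups the between-group variance is poorly estimated. With one group it cannot be separated from the treatment effect, and the conclusion must then be qualified. Chi-square comparisons need the same caveat.

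The cost is one recorded variable and revised analysis wording; treatment does not change. The price is wider confidence intervals and a lower stated power. Group membership should be recorded now, because recruitment has begun and it may be hard to recover later.
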